#### Secondary Endpoint

1.6.2

The secondary outcome will be differences in baseline QEEG features between the responder and non‐responder groups. By identifying responders prior to treatment, we can optimize resource allocation, minimize the time and cost associated with ineffective treatments, and ultimately improve the quality of care for individuals with MCI.

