
The rTMS intervention will be initiated 2 weeks after the EEG recording. On the first day, we will mark the stimulation site, specifically the left DLPFC, on the scalp using the 5.5 cm method. Another approach for localizing the left DLPFC is called the Beam F3 method. Many studies have declared that the effectiveness and reliability of these two methods in targeting the DLPFC are comparable (Pace et al. 2023; Trapp et al. 2023). We will conduct a total of 10 treatment sessions, with 1 session per day for 5 consecutive days over 2 weeks. Each session will involve delivering 2000 pulses at a frequency of 20 Hz, with a cycle of 2 s on and 28 s off, lasting a total of 25 min. We will target 100% RMT. These parameters were selected based on a recent review suggesting that they can produce the optimal clinical outcome (Lefaucheur et al. 2014). Trained PhD students in neuroscience will continuously monitor rTMS sessions, including pulse rate, respiratory rate, and any adverse events.

We target the DLPFC because it is a key region for higher‐level cognition, and its pathological damage leads to a characteristic feature of MCI (Yan et al. 2023; Xie et al. 2021). Moreover, it plays a crucial role in some major brain networks, such as the central executive network (CEN) and the fronto‐parietal network (FPN), indicating that the left DLPFC is the most effective site to improve global cognition outcomes (Opitz et al. 2016; Agosta et al. 2012).

The SimNIBS‐3.2 toolbox was applied to investigate the efficacy of the electric field produced by rTMS through the left DLPFC under our protocol (Figure 2) (Thielscher et al. 2015).

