#### Questionnaires

1.4.1

After 10 rTMS sessions, we will perform the cognitive tests again under the same conditions. For educated individuals, we will use MoCA exams, and for uneducated subjects (0 years of schooling), we will only use the MMSE test again. If a participant's MMSE or MoCA score increases after the TMS, they will be considered a responder. Conversely, if their score decreases or there are no changes, they will be classified as a non‐responder (Kayasandik et al. 2022).

We will utilize the minimal clinically important difference (MCID) to evaluate significant changes in test scores. According to the MCID, an increase of 3 points or 10% (Borland et al. 2022; Watt et al. 2021) in the MMSE indicates cognitive improvement (Borland et al. 2022; Watt et al. 2021). The MCID for the MoCA may vary, but we will consider a 1‐point increase as a sign of cognitive improvement (Lindvall et al. 2024). After completing the work, patients will receive free visits from the psychosomatic fellowship to continue their treatment in accordance with ethical principles.

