#### Primary Endpoint

1.7.1

All assessors will be blinded to group allocation and receive data labeled as “group A” and “group B.” Statistical analyses will be conducted using StataNow18.5 (Stata Corp, College Station, TX, USA), adhering to CONSORT guidelines. Normality of continuous variables will be checked using skewness and kurtosis, with variables considered non‐normal if absolute skewness > 2 or kurtosis > 3. Baseline characteristics, including (sex, hyper‐lipidemia, hypothyroid, hyper‐tension, diabetes, smoking, ischemic heart disease, education, and age) will be compared between groups using Fisher's exact test for categorical variables and the Mann–Whitney *U* test for non‐normal continuous variables. For normally distributed continuous variables, between‐group comparisons will be performed using the independent samples t‐test.

Initially, paired *t*‐tests (a suitable transformation or non‐parametric test) or equivalents for non‐normal data will be used to evaluate overall pre‐ to post‐rTMS changes within all 25 participants, assessing global treatment efficacy and identifying cognitive subdomains demonstrating the greatest response. Subsequently, participants will be categorized into responders and non‐responders based on MCID criteria. Between‐group comparisons of cognitive scores and subdomains will then be performed using ANOVA for baseline and ANCOVA for post‐intervention outcomes, adjusting for baseline scores and potential confounders. Pre‐intervention values refer specifically to baseline cognitive test scores, totally and in each cognitive sub‐domain, and related continuous variables measured before rTMS, which serve as covariates in the analyses. The QEEG features are analyzed separately as part of the secondary endpoint assessment. For non‐normal variables, suitable transformation will be applied, and median differences with percentage changes reported. Marginal plots from ANCOVA will visualize adjusted group differences post‐intervention. This two‐stage analytical approach allows comprehensive evaluation of rTMS effects both globally and within clinically meaningful responder groups across cognitive domains.

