#### Secondary Endpoint

1.7.2

Topographic maps will be generated for each QEEG feature (e.g., absolute power, relative power, power ratio, peak frequency, amplitude asymmetry, coherence, and phase lag) for both responder and non‐responder groups using Neuro Guide software, then calculate the average QEEG features for each group using Neuro Guide. Subsequently, the statistical significance of the dissimilarity between the two groups' EEG topographic maps will be determined using independent *t*‐tests or the Mann–Whitney *U* test, depending on the normality of the variables. ROC analysis estimating Area Under the Curve (AUC), sensitivity (SN), specificity (SP), positive predictive value (PPV), negative predictive value (NPV), A positive likelihood ratio (LR+), and the negative likelihood ratio (LR‐) for optimal cut‐points, as well as comparing AUC across biomarkers, will be performed using Stata 18 software. These diagnostic accuracy measures specifically assess the predictive ability of QEEG biomarkers in distinguishing responder from non‐responder status.

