Research has indicated that in cases of mild dementia, there is an increase in the theta brainwave band coupled with a decrease in the beta brainwave band. As dementia progresses, this pattern is further characterized by an increase in the delta brainwave band and a decrease in the alpha brainwave band (Gandelman‐Marton et al. 2017). The increase in the delta brainwave band corresponds to the white matter shrinking in the frontal region of patients with MCI and Alzheimer's disease (Babiloni et al. 2006). Additionally, the reduction of the alpha brainwave band occurs in the parietal, occipital, and temporal regions, in line with hippocampal shrinkage in MCI and Alzheimer's patients (Babiloni et al. 2009). Furthermore, the use of acetylcholinesterase inhibitors in dementia and Alzheimer's treatment leads to a reduction in the delta and theta brainwave bands (Jelic et al. 1998). Progression of disease and the failure of pharmacological treatments are associated with an increase in the delta and theta brainwave bands and a decrease in the alpha and beta brainwave bands (Jelic et al. 1998). Patients with Alzheimer's disease also show an increase in low‐frequency brainwave band power and a decrease in high‐frequency brainwave band power (Baggio et al. 1991). Additionally, there is a significant decrease in coherence in the theta, alpha, and beta brainwave bands in the frontal regions, which is consistent with the loss of neurons and disconnection of neocortical neurons (Besthorn et al. 1994).

Previous research with similar objectives has shown that patients with reduced levels of consciousness exhibit a higher absolute power of alpha waves in both the left and right parietal regions, which is associated with a greater likelihood of responding to rTMS (He et al. 2020). Additionally, in patients with severe dementia, the difference in the theta band has been observed as a predictor for respondents (Kayasandik et al. 2022). However, these studies differ from ours in terms of the stimulation parameters, including the stimulation site and disorder. Our findings will contribute to the development of correct prescription of rTMS therapy for MCI patients.

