Besides, there are some limitations to this protocol study. As an open‐label trial, it is subject to significant confounds, including treatment expectations on the part of participants, but this is a methodological limitation intrinsic to an open‐label trial (Thase 2001). For the future direction, more analysis with a larger dataset will be recommended, and randomized, sham‐controlled study can affect the generalizability and reliability of the outcomes. Additional predictive biomarkers such as genetic factors, neuroimaging, or biochemical biomarkers can be noticed in future study.

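### With one open-label arm, a baseline QEEG difference between participants whose scores rose and the rest cannot show who benefits from rTMS, so the treatment-selection statements should be restated as association

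*Protocol article*

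**What the plan says.** Every participant is treated (1.3.1: "We will conduct a total of 10 treatment sessions"), and no sham, untreated or waiting-list arm is described. The first analysis in 1.7.1 looks at pre-post "changes within all 25 participants, assessing global treatment efficacy and identifying cognitive subdomains demonstrating the greatest response". Sections 1.4.1 and 1.5 then define a responder by the change between the screening score and the score after ten sessions. On the MoCA "we will consider a 1‐point increase as a sign of cognitive improvement"; on the MMSE the rise must be 3 points or 10%.

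The secondary endpoint in 1.6.2 compares baseline QEEG between the two groups, and its next sentence draws the clinical consequence: "By identifying responders prior to treatment, we can optimize resource allocation, minimize the time and cost associated with ineffective treatments". The Abstract repeats that sentence under Outcome, and its Aims speak of sparing non-responders wasted treatment. The Discussion says: "Our findings will contribute to the development of correct prescription of rTMS therapy for MCI patients". Section 1.7.2 adds ROC measures and says: "These diagnostic accuracy measures specifically assess the predictive ability of QEEG biomarkers", completing the sentence with a reference to telling responders from non-responders.

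There are caveats. The introduction calls the study an exploratory pilot. The Discussion concedes: "As an open‐label trial, it is subject to significant confounds, including treatment expectations on the part of participants", and recommends a larger, randomized, sham-controlled study. The Limitations section calls the findings preliminary because the sample is small, the groups may be unbalanced and power is limited.

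**The concern.** Deciding whom to treat requires knowing whether the effect of rTMS differs by QEEG feature, which is a feature-by-treatment interaction. This design observes only what happens to treated people. A feature may separate those whose scores rose from those whose scores did not because it marks:

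- natural course;
- better learning when the same test is repeated, here after roughly four weeks (EEG the day after screening, rTMS two weeks later, two weeks of sessions);
- a usual cognitive level that differs from the screening score, so that the second score drifts back towards it.

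The last is plausible because participants enter through a three-point window on the same tests (MoCA 23 to 25 or MMSE 21 to 23), and the screening score is the only pre-treatment score described. None of the three is a reason to give or withhold rTMS. The stated caveats do not reach this problem. Those in the Limitations section suggest that a larger study would settle matters, but a larger single-arm study would only estimate the same ambiguous quantity more precisely.

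**Working it through.** The document gives no figure to reproduce: N = 25 is stated without an effect size, SD or power. The check is therefore about what the design can identify, with two illustrations. Retest SD, practice gain and the correlation ρ are assumptions and are not in the documents.

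**1. Identification.** Let x be a standardized QEEG feature. Among treated participants, the slope of score change on x is

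observed slope = slope without treatment (prognostic) + extra slope due to rTMS (interaction).

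A single arm supplies one equation for two unknowns. Suppose the observed slope is 1.0 point per SD of x. Then 1.0 + 0 (no selection value) and 0 + 1.0 (all selection value) fit the data equally well.

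**2. What the planned ROC analysis would show for a purely prognostic feature.** Model: change = 0.5 + b + 2 × [ρx + √(1 − ρ²) e], rounded to whole points, with responder meaning a change of at least 1. Here 0.5 is an assumed practice gain, 2 an assumed SD of change, and b the rTMS effect, the same for everyone. Because b does not depend on x, the feature has no value for choosing whom to treat. Simulated results:

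| ρ | AUC, b = 0 | AUC, b = 1 | P(p < 0.05), 25 patients, b = 0 |
|---|---|---|---|
| 0 | 0.50 | 0.50 | 5% |
| 0.3 | 0.64 | 0.64 | 20% |
| 0.5 | 0.73 | 0.74 | 53% |
| 0.6 | 0.78 | 0.79 | 73% |

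The last column is for a t-test on one feature. The AUC is nearly the same whether rTMS does nothing or helps everybody by one point, so it carries no information about benefit. The row ρ = 0 shows that score variation unrelated to the feature produces no systematic marker.

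**3. How often the responder rule is met with no rTMS effect.** For whole-point scores, with mean practice gain m and SD of change s:

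P(MoCA change ≥ 1) = 1 − Φ((0.5 − m)/s).

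| m | s = 1.5 | s = 2.0 | s = 2.5 |
|---|---|---|---|
| 0 | 0.369 | 0.401 | 0.421 |
| 0.5 | 0.500 | 0.500 | 0.500 |
| 1.0 | 0.631 | 0.599 | 0.579 |

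The range is 37% to 63%. If all 25 took the MoCA, that is 25 × 0.369 = 9.2 to 25 × 0.631 = 15.8 participants.

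For the MMSE, 10% of a baseline of 21 to 23 is 2.1 to 2.3, so both forms of the rule require 3 whole points. P(change ≥ 3) = 1 − Φ((2.5 − m)/s) runs from 0.048 (s = 1.5, m = 0) to 0.274 (s = 2.5, m = 1) over the same inputs.

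**The case against.** The protocol is more careful than its benefit sentences suggest. A reader might infer that it promises QEEG will identify who benefits. Mostly it states an aim, the introduction only aspires to better allocation, and the Conclusion ends by asking whether features differ between those who improved and those who did not. The endpoint itself, apart from the sentence that follows it, is a plain comparison. The Discussion already recommends the missing sham control, and the Limitations section rules out definitive hypothesis testing. All of this stands, and it makes the point one of wording for a pilot, with no call for redesign.

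A reader might also take 1.7.2 as claiming prediction of benefit. Read to its end, the sentence claims only discrimination of responder status, which ROC measures do assess. The analysis can stay.

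Two further inferences should be resisted. Pure retest noise does not create a misleading marker: if unrelated to QEEG, it misclassifies responders and weakens any association. And the 37% to 63% range does not measure the marker problem. It describes chance response under the MoCA rule, rests on assumed inputs, and is lower under the MMSE rule that applies to participants without schooling.

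What the objection does not remove is that no part of the document mentions practice, regression to the mean, or the difference between a prognostic marker and one that predicts benefit. The sentences in the Aims, Outcome, 1.6.2 and the Discussion remain without that qualification.

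**Conclusion.** The point holds as a mismatch between claim and design. The treatment-selection statements in the Abstract (Aims and Outcome), 1.6.2 and the Discussion attribute to the study something a single open-label arm cannot show, at any sample size and for any AUC. This follows from the absence of a comparator and needs no numerical assumption. The figures only illustrate it: at ρ = 0.5 an AUC of 0.73 or 0.74 arises from a feature with no selection value, given an assumed SD of 2 and practice gain of 0.5.

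The document does not support going further and saying that the pilot would lead to rTMS being withheld from people who would benefit, since it commits to cautious, preliminary interpretation and to later confirmatory work. Regression to the mean would raise the responder rate only if usual scores in the screened population tend to lie above the entry window, which the document does not tell us.

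**What to change.** - **Abstract (Aims, Outcome), 1.6.2 and Discussion:** replace the selection and resource-allocation statements with wording such as *baseline QEEG features associated with short-term score gain after open-label rTMS, hypothesis-generating; whether they predict benefit from rTMS cannot be assessed without a control arm*. The closing sentence of the Conclusion is already close to this.
- **1.7.2:** keep the ROC measures, and state that they describe discrimination of score-gain status, not of treatment benefit.
- **Limitations paragraph at the end of the Discussion:** beside expectation, add practice effect, regression to the mean, and misclassification from retest error under the 1-point MoCA rule. Note that the recommended sham-controlled study would need a feature-by-arm interaction test.

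The cost is a less favourable claim. No patients, visits, data or analyses are added.

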### Statistical Methods

1.7

#### Primary Endpoint

1.7.1

All assessors will be blinded to group allocation and receive data labeled as “group A” and “group B.” Statistical analyses will be conducted using StataNow18.5 (Stata Corp, College Station, TX, USA), adhering to CONSORT guidelines. Normality of continuous variables will be checked using skewness and kurtosis, with variables considered non‐normal if absolute skewness > 2 or kurtosis > 3. Baseline characteristics, including (sex, hyper‐lipidemia, hypothyroid, hyper‐tension, diabetes, smoking, ischemic heart disease, education, and age) will be compared between groups using Fisher's exact test for categorical variables and the Mann–Whitney *U* test for non‐normal continuous variables. For normally distributed continuous variables, between‐group comparisons will be performed using the independent samples t‐test.

Initially, paired *t*‐tests (a suitable transformation or non‐parametric test) or equivalents for non‐normal data will be used to evaluate overall pre‐ to post‐rTMS changes within all 25 participants, assessing global treatment efficacy and identifying cognitive subdomains demonstrating the greatest response. Subsequently, participants will be categorized into responders and non‐responders based on MCID criteria. Between‐group comparisons of cognitive scores and subdomains will then be performed using ANOVA for baseline and ANCOVA for post‐intervention outcomes, adjusting for baseline scores and potential confounders. Pre‐intervention values refer specifically to baseline cognitive test scores, totally and in each cognitive sub‐domain, and related continuous variables measured before rTMS, which serve as covariates in the analyses. The QEEG features are analyzed separately as part of the secondary endpoint assessment. For non‐normal variables, suitable transformation will be applied, and median differences with percentage changes reported. Marginal plots from ANCOVA will visualize adjusted group differences post‐intervention. This two‐stage analytical approach allows comprehensive evaluation of rTMS effects both globally and within clinically meaningful responder groups across cognitive domains.

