**Design:**

This multi‐center, assessor‐blinded clinical trial will examine QEEG biomarkers as predictors of rTMS treatment responsiveness in 25 patients with mild cognitive impairment (MCI). Adults aged 60 years or older will undergo cognitive assessments using the Montreal Cognitive Assessment (MoCA) or mini‐mental state examination (MMSE) and have an electroencephalography (EEG) recording. Participants will complete 10 rTMS sessions targeting the left DLPFC over 2 weeks, with 2000 pulses per session at 20 Hz. Cognitive tests will be repeated post‐treatment, and participants will be classified as responders or non‐responders based on cognitive changes, then baseline QEEG parameters will be compared between the two groups. The primary endpoint is the proportion of responders at ten sessions after rTMS (score post‐intervention > score pre‐intervention = responder, according to the minimal clinically important difference (MCID) threshold (i.e., an increase of at least 3 points or 10% on the MMSE, or an increase of at least 1 point on the MoCA); score post‐intervention ≤ score pre‐intervention = non‐responder). The secondary endpoints are the differences in baseline QEEG features between responders and non‐responders.

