We will record the participants' EEG data using a 19‐channel EEG system with passive electrodes (Science Beam; Parto Danesh Co., Iran). It has 19 scalp channels, a sampling rate of 500 Hz per channel, an ADC resolution of 24 bits, and a CMRR of 75 dB at 500 Hz. The electrode placement will follow the 10–20 international norm and referential montage linked ears. Every subject had a 5‐minute resting‐state EEG recording with their eyes open, followed by a 5‐min recording with their eyes closed, all while maintaining an impedance of less than 10 kΩ and applying a 0.5 low‐cut and a 500‐Hz high‐cut filter.

Finally, after the automated algorithm, manual checking by an expert neuroscientist for the artifact rejection process. Topographic maps will be generated for each QEEG feature in the frequency domain (e.g., absolute power, relative power, power ratio, peak frequency, amplitude asymmetry, coherence, and phase lag) for both responder and non‐responder groups using Neuro Guide software version 3.2.1.1 (Loo et al. 2016; Coburn et al. 2006).

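### The only assessor blinding described, A/B group labels, cannot protect the cognitive rating that decides the primary endpoint, because that rating creates the groups

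*Protocol article*

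**What the plan says.** The title, the abstract and section 1 (Study Design) describe an assessor-blinded trial; the title also says open-label. The only mechanism given is in section 1.7.1, under the primary endpoint: "All assessors will be blinded to group allocation and receive data labeled as" group A and group B.

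The design is a single treated cohort. The abstract says "Participants will complete 10 rTMS sessions targeting the left DLPFC over 2 weeks", and section 1.7.1 first tests pre- to post-rTMS "changes within all 25 participants, assessing global treatment efficacy". Groups come next: "Subsequently, participants will be categorized into responders and non"-responders. Section 1.4.1 defines them by the change in score: if the MMSE or MoCA "score increases after the TMS, they will be considered a responder", with MCID thresholds of 1 point on the MoCA and 3 points or 10% on the MMSE. On how the second test is given, section 1.4.1 says "After 10 rTMS sessions, we will perform the cognitive tests again under the same conditions".

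Section 1.6.1 makes the share of participants who meet the MCID rule the primary endpoint. The Discussion concedes confounding from participants' expectations in an open-label trial and leaves a sham-controlled study to the future.

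**The concern.** A reader takes assessor-blinded to mean that whoever scores the outcome is shielded from knowledge that could sway the score. In a randomised trial, masking to allocation does this. Here there is no allocation, and the groups do not exist until the second test has been scored. The stated protection therefore does not reach the measurement behind the primary endpoint.

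This matters because the MoCA threshold is a single point on a 30-point scale, so a small average leniency at the second visit can move participants near the boundary into the responder group. The same labels then feed the baseline QEEG comparison and the ROC analysis in section 1.7.2. Rater expectation is not among the limitations that the article names.

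**Working it through.** **Order of events**

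1. Baseline MoCA or MMSE at screening; EEG the next day (sections 1.1.1 and 1.1.2).
2. rTMS begins two weeks after the EEG and runs for 10 sessions over two weeks, for everyone (section 1.3.1).
3. Post-treatment MoCA or MMSE is scored (section 1.4.1).
4. The change in score sets responder or non-responder status (sections 1.4.1 and 1.5).
5. Data can now be labelled A and B (section 1.7.1).

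The label in step 5 is a function of the score in step 3, so it cannot mask step 3. Masking the tester would mean hiding the visit, the receipt of treatment or the baseline score. The article describes none of these.

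After step 5 the labels can do some work, for example for a person who processes EEG or runs the QEEG comparison. They do less in the cognitive comparison of section 1.7.1. The groups are defined by gain, so the group with the larger gains reveals itself as the responders.

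**Illustration of size**

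The article gives no SD, effect size or power figure behind the 25 participants, so there is no stated figure to reproduce. Thresholds come from section 1.4.1. The following are assumptions: no true change, a normally distributed change score rounded to whole points, SD from 1 to 3, and a mean rater shift *m* of 0, 0.5 or 1 point.

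P(gain of at least *k*) = 1 − Φ((*k* − 0.5 − *m*) / SD)

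For the MoCA *k* = 1. For the MMSE *k* = 3: on eligible baseline scores of 21 to 23, 10% is 2.1 to 2.3 points, which also needs 3 whole points.

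| Test | SD | *m* = 0 | *m* = 0.5 | *m* = 1 |
|---|---|---|---|---|
| MoCA, gain ≥ 1 | 1 | 0.309 | 0.500 | 0.691 |
| | 2 | 0.401 | 0.500 | 0.599 |
| | 3 | 0.434 | 0.500 | 0.566 |
| MMSE, gain ≥ 3 | 1 | 0.006 | 0.023 | 0.067 |
| | 2 | 0.106 | 0.159 | 0.227 |
| | 3 | 0.202 | 0.252 | 0.309 |

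Worked example, MoCA with SD 2: 1 − Φ(0.5/2) = 0.401 with no shift, and 1 − Φ(−0.5/2) = 0.599 with a shift of 1 point.

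If all 25 took the MoCA, the expected number of responders with no shift is 25 × 0.309 = 7.7 to 25 × 0.434 = 10.8. With half a point of leniency it is 25 × 0.5 = 12.5. The increase is 12.5 − 10.8 = 1.7 to 12.5 − 7.7 = 4.8, or about 2 to 5 participants.

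**The case against.** Several replies have force.

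- **Some blinding is possible.** The sentence in section 1.7.1 is about people who receive labelled data, so they act after classification and can be masked to responder status. This stands. A reader might infer that no blinding can exist in this trial at all; the documents do not support that. The gap concerns the cognitive rating.
- **The tester is not identified.** The article does not say who gives the second test, or that this person is one of the assessors in section 1.7.1. Screening is at the hospital and rTMS at a clinic, so separate staff are compatible with the text. This also stands: one cannot say that the tester will know the baseline score or has a stake in the result. But no masking of the tester is described, and if the assessors are only data handlers, the label in the title has no support for the primary endpoint.
- **EEG cleaning.** Section 1.2.2 provides for "manual checking by an expert neuroscientist for the artifact rejection process". A reader might infer that this is done with response status known. No passage plans that: EEG precedes rTMS, and section 1.2.2 places cleaning before the group maps. An article may also leave processing order to a fuller protocol. Locking the EEG is therefore a safeguard, not the repair of an error.
- **Open-label bias is partly disclosed.** The title says open-label, and the Limitations section calls the findings preliminary. This softens the consequence. It does not make the blinding statement correct.
- **Effect on the biomarker aim.** Leniency unrelated to a patient's EEG would tend to dilute QEEG differences rather than create them. That is fair; the responder rate and the overall pre-post tests are what it would inflate.

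**Conclusion.** The blinding statement is wrong as written for the primary endpoint. In a single-arm study whose groups are made from the outcome, masking to group allocation has no meaning when the outcome is rated, and A/B labels can mask only those who handle data afterwards. This conclusion follows from the order of events and needs no assumption.

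The size does rest on assumptions. With an SD of 1 to 3 points and no true change, a mean leniency of half a point takes the MoCA responder rate from 31–43% to 50%, and a full point takes it to 57–69%. The MMSE rule is less exposed in absolute terms: about 1–20% with no shift and 7–31% with a full point. A shift relabels only participants near the boundary. The 31–43% with no shift reflects retest noise against a 1-point threshold, not a failure of blinding. The documents give no evidence that such a shift will occur, only that the described masking would not prevent it.

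**What to change.** Replace the blinding sentence in section 1.7.1 with a statement of who is masked to what:

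- All participants receive rTMS and no groups are allocated.
- EEG processing and data analysis are done without knowledge of responder status.
- The primary cognitive outcome is not claimed as blinded outcome assessment, unless masking of the tester is in place and described.

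Carry the same qualification wherever the design is called assessor-blinded, and add rater expectation to the limitations beside participant expectation.

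Two safeguards are worth adding. First, finish and lock artifact rejection and QEEG feature export before any post-treatment score is released to the EEG team. The EEG is recorded two weeks before rTMS and treatment lasts two weeks, so about four weeks are available. Second, withhold the baseline score from the post-visit tester where existing staffing allows. This will not hide that it is the second visit, so it reduces anchoring without making the rating blinded. Baseline forms must be scored at screening because they determine eligibility, so joint scoring of pre and post forms at the end should not replace that step.

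The cost is wording, one data-lock step and minor logistics.
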